## Abstract

**Background:**

Mental health issues in youths have cascading negative effects on school outcomes, professional life, and physical health. Psychological well-being (P-WB) is an important protective factor against mental illness. Preliminary research suggests that mindfulness- and yoga-based socio-emotional learning (SEL) interventions can each have a positive impact on preschoolers P-WB. The objective of this trial is to rigorously evaluate the effect of a 24-week combined mindfulness- and yoga- based SEL intervention in preschool children from a French socio-economically disadvantaged area.

**Methods:**

The P-WB promotion intervention is compared to a wait-list control condition in a cluster randomized controlled trial (RCT). Sixty-four pre-Kindergarten classrooms are randomized to the intervention or control group. Primary outcomes measure self-management capacity and core P-WB components: connection, insight, engagement, and positive relationship. Secondary outcomes include measures of mental health, executive functioning, and school performance. Primary and secondary outcomes are assessed through teacher questionnaires, standardized observations of children in school context, and experimental tasks and by collecting results of the national evaluation at first grade. All children-level outcomes are evaluated at pre-intervention, at the end of the intervention, and 1 year later (follow-up analysis), to the exception of school performance which is evaluated at follow-up only. Intention-to-treat analyses, accounting for clustering within classes, will adopt a random effects linear regression model to examine outcomes for the intervention versus control children.

**Discussion:**

This is the first trial to rigorously evaluate a combined mindfulness- and yoga-based P-WB promotion intervention, and the first RCT evaluating a SEL curriculum in French schools. Results may have key implications for P-WB promotion in preschool children.

**Trial registration:**

https://www.drks.de/ DRKS00028623. Retrospectively registered on 30 May 2022

**Supplementary Information:**

The online version contains supplementary material available at 10.1186/s13063-022-06979-2.

## Administrative information

Note: the numbers in curly brackets in this protocol refer to SPIRIT checklist item numbers. The order of the items has been modified to group similar items (see http://www.equator-network.org/reporting-guidelines/spirit-2013-statement-defining-standard-protocol-items-for-clinical-trials/).

## Introduction

### Background and rationale {6a}

Mental health issues are common in children and adolescents: psychiatric disorders affect at least one in ten 5-to-16-year-old youths [19], and 50% of all lifetime mental illness begins by age 14 [49]. Emotional and behavioral problems that are not part of a diagnosed disorder are even more common, and their rates have increased over the past 30 years in several countries [19], with a recent dramatic peak due to the COVID-19 pandemic [57, 63]. Mental health issues in youths can have cascading effects over time on school and professional outcomes, contributing to a major economic burden [33]. In this context, reinforcing public action to promote mental health in youths has recently been described by the American Academy of Pediatry as a “national emergency” [4].

Psychological well-being (P-WB) is a multidimensional construct whose definition remains a matter of debate [31]. According to the PERMA framework, P-WB in youths can be measured based on five core facets of self-evaluation: *Positive Emotions*, the tendency to experience hedonic feelings of happiness; *Engagement*, the psychological connection to activities or institutions; *Positive Relationships*, the feeling of being socially integrated, cared about and supported by others; *Meaning,* the belief that one’s life is valuable; *Accomplishment*, the feeling of being capable of making progress and of achievement [48]. Decades of observational and interventional research have linked measures of youths and adults’ P-WB to health outcomes, as well as to educational and professional achievement [18, 30, 82]. While measures of P-WB are partly independent from measures of mental illness, research suggests that psychological well-being is an important protective factor for mental disorders [45, 50, 70, 85].

Gathering children from various backgrounds for a substantial daytime, school context constitutes a preferential context for P-WB promotion through socio-emotional learning (SEL [4];). At the individual level, a recent model identified 4 skills central to P-WB (P-WB skills): *Awareness*, defined as an heightened and flexible attention to perceptual impressions and internal cues such as thoughts or emotions; *Connection*, a subjective sense of care and kinship toward other people; *Insight*, a self-knowledge concerning the manner in which emotions, thoughts, and beliefs contribute to one’s subjective experience; *Purpose*, a sense of clarity concerning personally meaningful aims and values [24]. Beyond these four specific skills, it is probable that other related individual competencies are important for children’s P-WB. Socio-emotional competencies (SEC) designate the set of social and emotional abilities necessary to function effectively in social context and deal efficiently with the social and emotional challenges of everyday life [17]. The Collaborative for Academic, Social and Emotional Learning (CASEL) framework, one of the dominant SEC frameworks, identifies five core SEC. Among these, *Self-management*, the ability to regulate one’s emotions, stress, impulse, thoughts, and behaviors, has been identified as a key predictor of school engagement [72] and school achievement [51, 78], suggesting a strong impact on the P-WB *Engagement* dimension. Given the key relationship between *Self-management* and school readiness, SEL interventions targeting P-WB skills and *Self-management* in preschool years may have unique developmental leverage [10].

Among the various approaches available to promote P-WB, mindfulness-based interventions (MBIs) have demonstrated the greatest efficacy in both clinical and non-clinical populations [79]. Mindfulness describes both a mental faculty (a “trait”) and a practice implying deliberate conscious awareness of the present moment, including meta-cognitive awareness of present thoughts or emotions without judgment [37, 69]. Directly targeting the *Awareness* component of P-WB skills, mindfulness practice is also thought to contribute indirectly to the three other core P-WB skills—that is *Connection, Insight*, and *Purpose* [76]. Moreover, constructs measured to evaluate MBIs in a school context overlap conceptually with core competencies of the CASEL SEC framework—especially *Self-management*, and MBIs have been found to enhance *Self-management* capacity [36]. Along MBIs, yoga-based interventions (YBIs) have been identified as promising P-WB promoters. Focused on controlled breathing, body movements, and postures, yoga shares with mindfulness practice a direct focus on *Awareness*, while also providing a space to develop *Self-management* skills [76]. In youths, MBIs have been found to promote executive functioning and attention (two key contributors to *Self-management* competency) and to reduce depression, anxiety/stress, and negative behaviors [35], while YBIs were found to reduce anxiety [80]. Effects of yoga breathing practices are reflected in changes in functional brain connectivity and changes in the activity of brain regions involved in emotion processing [59]. In preschoolers, preliminary studies suggest that mindfulness and yoga practice positively impact several components of executive functioning (visual attention, sustained attention, inhibition), *Self-management* capacity, and pro-social behavior, while diminishing externalizing symptoms [64, 73].

In sum, a strong evidence-base for MBIs exists in the overall P-WB promotion field, along with promising data for YBIs. Nonetheless, recent literature reviews have underlined that available studies of MBIs in school-aged children are characterized by important methodological limitations [37, 67]. Most studies were conducted in small samples, few integrated independent blind observer ratings, and studies were each devoted to testing new mindfulness-based protocols rather than replicating previous findings [67]. In preschoolers more specifically, the current evidence-base for MBIs and YBIs can only be considered preliminary, as the limited number of studies available present a methodological risk of bias, with a majority presenting a high level of risk [73].

MBIs and YBIs share common targets [76], and yoga practice has been found to promote a mindfulness state [68], suggesting that combining mindfulness and yoga practice may have a synergistic impact. While two studies from a research group examined the effect of mindful yoga in preschoolers ((Razza et al. [65, 66]), to our knowledge, no study to date evaluated the effect of an intervention combining separate yoga-based and mindfulness-based activities. Furthermore, previous studies examining MBIs and YBIs often evaluated interventions delivered by specialized instructors [73]. While having external trainers delivering programs may maximize intervention quality, it can represent a major obstacle to countrywide systemic dissemination. Teacher training represents a less costly alternative and a facilitator for dissemination, while integration of mindfulness- and yoga-based activities into teacher curriculum may have a positive impact on teacher-student relationships [11].

Considering the need to improve the evidence-base for early P-WB promotion in preschoolers through replication studies with minimal risk of methodological bias, the present study was designed to rigorously evaluate a mindfulness- and yoga-based SEL curriculum delivered by trained teachers in preschools in France. While PISA studies have repeatedly found delays in SECs in French students [2], evidence-based SEL programs adapted to the national context are currently lacking. The mindfulness-based SEL protocol was adapted to the national context based on a program targeting the *Awareness*, *Connection*, and *Insight* P-WB skills, which was found to positively impact social competence and engagement in learning in a previous randomized controlled trial (RCT) [38], and delivered as part of a broader SEL curriculum integrating yoga-based activities and an emotion circle time targeting the *Insight* and *Connection* components of P-WB. Given the strong association between socio-economic status and self-management [58] or P-WB [62], we chose to deploy and evaluate this intervention in a predominantly socio-economically disadvantaged French department.

## Objectives {7}

This trial evaluates the impact of an incremental P-WB curriculum delivered in French preschools, (1) after 24 weeks of program exposure in children 4 to 5 years old (during *moyenne section* in France: US Pre-K equivalent) and (2) 1 year later (end of *grande section:* US kindergarten equivalent; follow-up analysis).

Our primary objective is to assess the effects of the curriculum on P-WB-related measures of *Connection, Insight*, *Engagement*, *Positive Relationships*, and *Self-management*. Our secondary objective is to document the effects of the curriculum on measures of mental health, executive functioning, and school performance [51]. We hypothesize that the intervention will lead to more favorable outcomes on P-WB, mental health, and executive functioning measures after 24 weeks of program exposure, that these effects will be maintained 1 year later, and that school performance at the national evaluation 2 years later will be superior in children who received the intervention compared to the control group.

We also investigate heterogeneous effects according to teacher-level and children-level characteristics. In terms of teacher-level characteristics, we first investigate heterogeneity according to teacher P-WB since higher levels of P-WB are associated with higher impacts in various interventional settings [25, 47, 52, 75]. Second, we will use a machine-learning model to assess potential heterogeneous effects of the curriculum according to the teachers’ level of commitment in implementing the intervention (see the “Methods for additional analyses (e.g., subgroup analyses) {20b}” section for additional details). Higher levels of fidelity of implementation are associated with higher gains in children’s P-WB, mental health, and executive functioning [40, 56]. In terms of children-level characteristics, we investigate heterogeneity according to the initial levels of EF, *connection*, and problem behaviors. Lower pre-intervention levels of EF and *connection* are associated with higher gains in EF [38, 73] and *connection* [73] respectively. Similarly, higher pre-intervention levels of problem behaviors are associated with higher reductions in post-intervention problem behaviors [38].

## Trial design {8}

The trial described in this protocol is a superiority two-armed cluster randomized controlled trial designed to evaluate the value-added of a P-WB promotion curriculum for pre-K children delivered by teachers, compared to teaching as-usual. Sixty-four pre-K classrooms from 50 different schools are randomly allocated to the intervention group or to the control group. In France, preschool classes can either include only students from one school year (here, Pre-K students only, “*moyenne section*” corresponding to 4-year-old children on average) or a mixture of children from Pre-K and kindergarten levels (kindergarten, hereafter K, students, or “*grande section*”, correspond to 5-year-old children on average). In the present sample, 36 classes included only Pre-K students, and 28 classes included a mixture of Pre-K and K levels students. In this context, as we expected potential differential effects according to the type of classroom, we stratified the sample by classroom type in order to compare treatment and control groups within the same type of classrooms. In practice, in the 36 classrooms with only Pre-K students, we randomly assigned 18 classrooms to the treatment group and 18 classrooms to the control group. In the 28 classrooms with a mix of Pre-K and K students, we assigned 14 classrooms to the treatment group and 14 classrooms to the control group. Overall, the treatment group and the control group are both composed of 32 classrooms.

## Methods: participants, interventions, and outcomes

### Study setting {9}

The study was conducted in public schools from sixteen municipalities of the *Seine-Saint-Denis* French department (93) (*Ile-De-France* region, France). The 93 department has the highest poverty rate of metropolitan France, placing this trial in a relatively high poverty context.

### Eligibility criteria {10}

*Inclusion criteria*: children at pre-K level (*moyenne section*) attending public schools.

*Exclusion criteria*: parent refusal for the child to participate in the study or consent withdrawal during the study.

*Specific exclusion criteria for collection of experimental data and observations*: (1) children showing comprehension difficulties in French language; (2) children with high difficulties in expressive French language or children who do not speak French; (3) children with suspicion of neurodevelopmental disorders (notably intellectual disability or Autistic Spectrum Disorder); (4) children with severe behavior problems (e.g., high aggression/tantrum level) whose teachers judged that taking part in the experimental part of the protocol would not be possible. These criteria were implemented to ensure that experimental data collection would be feasible with the selected children. Teachers were asked to exclude children based on this list of criteria.

### Who will take informed consent? {26a}

Informed consent is obtained from children’s parents, before starting the first evaluation session. Information letters with an attached reply form are posted to teachers at the beginning of the school year. Teachers then transmit these letters to parents. Parents who refuse participation for their child send the reply form back to the teacher, who then informs principal investigators of parent refusal [OC, TV]. In the information letter, (1) objectives, contents, and attended benefits of the intervention (if applicable) are described; (2) parents are told that participation of their child is entirely voluntary (i.e., parents can accept or refuse to participate to the study without any consequences), and (3) that they can withdraw their participation at any time by stating it to the teacher and/or returning the refusal reply form. Parents are not paid for their child participation in the study. Oral consent was obtained from children before experimental task data collection.

### Additional consent provisions for collection and use of participant data and biological specimens {26b}

N/A. No biological specimens are collected in this trial.

### Interventions

#### Explanation for the choice of comparators {6b}

Pre-K and kindergarten French programs do not include coherent SEL components targeting P-WB. Nonetheless, teachers sometimes decide to integrate some SEL activities on an autonomous basis. In this trial, children from classes receiving our structured and progressive P-WB promotion curriculum as part of their school year program are compared to children from waiting-list classes exposed to a “usual” school year. Teachers are randomly assigned to the intervention group or to the waiting-list control group. Teachers from the control group are told to teach their class as they would have any other year. Teachers allocated to the wait-list control group for the evaluation year (September 2021–June 2022) are proposed to follow the program training course the following year (September 2022–June 2023). Comparison to a wait-list control condition was chosen in this study to replicate intervention benefits, prior to studying the specificity of effect in future studies by comparing the P-WB promotion curriculum to active conditions. Allowing teachers to benefit from the program and materials 1 year later was deemed necessary to maximize recruitment chances in the context of the 93 French department and minimize the risk of control group disengagement from the study.

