##### Intervention group

The P-WB promotion intervention is composed of a set of activities delivered each week: (1) a mindfulness-based SEL curriculum, (2) ritualized yoga activities adapted for preschool children, and (3) a ritualized circle time. Teachers in the intervention group are asked to implement the P-WB curriculum during regular school hours after completion of the training course. They receive a 2-day training delivered by the principal investigator [TV, clinical psychologist trained in cognitive-behavioral therapy including mindfulness], a yoga-instructor, and a teacher with experience in delivering yoga-based activities to kindergarten classes. Training is based on role-play to directly experience teaching of P-WB activities and includes a personal initiation to mindfulness and yoga. Curriculum is set up to be delivered during 24 weeks. A guided instruction manual, with detailed descriptions of activities, objectives, timing, and contents is provided for each type of activity (kindness curriculum, yoga, circle time) along with all required material.*French adaptation of the Kindness Curriculum (KC):* The mindfulness-based SEL component of this curriculum is an adaptation of the KC developed by the Healthy Minds Innovations, Inc - Center for Investigating Healthy Minds, University of Wisconsin-Madison, USA [38]. The KC is a mindfulness-based SEL curriculum designed for preschool children (4 to 6 years) which aims at developing the *Awareness*, *Connection*, and *Insight* P-WB skills. Activities are detailed in a manual, are structured and progressive, and are based on books, music, and physical activities related to self-awareness, empathy, gratitude, and kindness [38].The KC has undergone prior scientific evaluation, demonstrating that it leads to positive outcomes on various indicators—sharing proneness, teacher-reported social competences, cognitive flexibility, self-regulation, and grades in preschool children—when delivered by trained mindfulness instructors [38]. Another pilot RCT tested delivery by teachers instead of instructors and found that preschool children that were allocated to an adapted version of the KC showed better attentional focus and self-regulatory skills compared to children in an as-usual condition, although no change in empathy or compassion were observed [61].French adaptation was undergone during a pilot study conducted with 8 kindergarten teachers between September 2019 and June 2021 [21]. Teachers were trained to implement the program and qualitative data (focus groups and personal interviews) were collected to assess program relevance and difficulties in implementation. Adaptation included modifying five books of the original program which were not available in France. Books targeting the same topics were found and tested. While the original version of the KC delivered by mindfulness instructors was designed to be implemented across 12 weeks with two 20–30-min sessions per week, our adapted version divided the KC lessons over the course of 2 years, from the beginning of pre-K to the end of kindergarten, with two 20–25-min sessions per week during a total of 48 weeks. Adaptations followed teacher requests during piloting, who agreed that sessions were excessively long, that the program would benefit from having the possibility to revise previous concepts and examine multiple times each topic. As a result, some lessons were split in two (e.g., the third lesson of theme 1 has been split in two parts, one dedicated to the “seeds of kindness” and the second part dedicated to the “follow me” game).The adapted French version retained the original division into eight global themes, with each theme divided into three lessons. The first themes (“theme 1: “mindful bodies and planting seeds of kindness”, theme 2: “I feel emotion of the inside”, theme 3: “how I feel on the inside shows on the outside”, and theme 4: “taking care of strong emotions on the inside and outside”) are covered during the Pre-K year, and the last themes (theme 5: “calming and working out problems”, theme 6: “gratitude”, theme 7: “all people depend on each other and the earth” and theme 8: “gratitude and caring for our world”) are covered during kindergarten after revising core Pre-K lessons. In the present evaluation, only the first 4 themes were covered (Pre-K year adaptation).As in the original program, each session is structured as follows: (1) *Introduction phase*. Teachers introduce the KC time, by initiating routine activities: reunion of children in circle, meditation bell ringing, and breathing exercises. (2) *Teaching phase*. Teacher introduces pupils with a new notion (e.g., pay attention, feelings, “peace wands” …), makes links between a previous lesson and the new one, reads a story, and asks questions about it (“why was the girl quiet?”). (3) *Active engagement phase*. Children put notions into practice and realize activities: role-playing (“peace wands”), planting seeds together, playing imitation game, practicing breathing exercises with bean bag animals …. (4) *Closing phase*. Teacher closes the lesson with a take-home message.Teachers are asked to deliver at least two 20–25-min lessons of the KC per week.*Yoga-based ritualized activities:* A yoga-based program was developed in collaboration with a professional yoga instructor and a kindergarten teacher experienced in delivering yoga activities to her classrooms. Teachers received a manual along with 30 “yoga cards” to implement activities devoted to six categories: warm-up, auto-massaging, exercises while sitting down (including breathing exercises), exercises while standing (postures), relaxation. Exercises were tailored during the pilot-study to be accessible for teachers without prior yoga practice.Teachers were given freedom to implement different activities in different sessions, but a typical order for one session was proposed, with the following steps:*Warm-up phase*. Children stretch themselves.*Massage phase*. Children massage themselves different parts of their body. Progressively, teachers introduce more body-linked vocabulary (e.g., “arm,” “elbow,” “forearm,” “wrist”…).*Postures and controlled-breathing phase*. Children learn to reproduce yoga postures (seated and standing) adapted for children and modeled by teachers. They also learn to become aware of their breathing and to control it.*Relaxation phase*. Children focus themselves on breathing and/or inside their body.Exercise level increases progressively throughout the year, with the first sequences mostly focused on introducing the activity and familiarizing children with it, using easy exercises and vocabulary.Teachers are asked to deliver at least 20–25 min of yoga-based activities per week, in a minimum of one session, and are encouraged to deliver everyday sessions to ritualize practice.*Emotion circle time:* A ritualized emotion circle time developed at Mons University, Belgium, completed the program [43]. Emotion circle time was added to the program to target the *Insight* and *Connection* components of P-WB. It follows a ritualized procedure to explore children’s emotions regarding a particular time of the day (typically recess) and finds solutions for children exposed to negative emotions. Children are asked to express their emotions individually by choosing between diverse “smiley” faces on a card (“happy,” “sad,” “fearful,” or “angry”). Then, teachers preferentially ask children who chose an emotion with negative valence to explain why they are feeling this. Three rules are used and recalled by children at the beginning of each session: (1) emotion cannot be denied by others; children use “I” statements and their feeling cannot be contradicted (e.g., “I feel… because…”); (2) teacher distribute speaking time (e.g., by giving and taking back a “talking stick”) and children speak one at a time; (3) children do not name or accuse others (they are asked to use the “someone” pronoun)—i.e., focus is put on finding solutions altogether and not on accusing others. Children discuss between themselves and with the teacher what could be implemented to help this child feel better. Finally, teachers remind children that this situation will be reexamined during the next session to monitor the evolution until the problem is resolved.Teachers are asked to deliver at least 20–25 min of emotion circle time per week, in a minimum of one session, and are encouraged to deliver everyday sessions to ritualize practice.

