### Participant timeline {13}

Outcome measures are collected before the start of the intervention (pre-K; October-November 2021, T0), at the end of the first year (May-June 2022; pre-K; T1), at the beginning of the second year for kindergarten teachers’ characteristics only (October 2022; kindergarten; T2), at the end of the second year (May-June 2023; kindergarten; T3), and at follow-up for school performance only (1st grade; September 2023 and March 2024; T4). Data are collected directly by principal investigators [OC] from computerized forms (questionnaires and scales), and by trained evaluators recruited for the study for tasks and observations. Tasks and observations take place in schools—in the classroom, hallways, and recess for observations, and in a dedicated room for experimental tasks.

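### Control teachers are offered the programme before T3 and T4, so follow-up may compare earlier with later access rather than programme with no programme

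*Protocol article*

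**What the plan says.** In the Protocol article, section {6b} names September 2021 to June 2022 as the evaluation year. It says that wait-list teachers "are proposed to follow the program training course the following year", that is, September 2022 to June 2023. The stated reason is practical: "Allowing teachers to benefit from the program and materials 1 year later was deemed necessary to maximize recruitment chances".

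Participant timeline {13} places the one-year assessment "at the end of the second year (May-June 2023; kindergarten; T3") and the national tests "at follow-up for school performance only (1st grade; September 2023 and March 2024; T4"). Objectives {7} hypothesises, for the first of these, "that these effects will be maintained 1 year later", and for the second, better school performance than in the control group.

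Trial design {8} reports that "28 classes included a mixture of Pre-K and K levels students", split 14 and 14 between the arms; the other 36 classes are pre-K only, 18 and 18. Recruitment {15} says that the enrolled teachers teach at pre-K level. The Intervention group section of {11a} says that the French adaptation "divided the KC lessons over the course of 2 years, from the beginning of pre-K to the end of kindergarten", but that this evaluation covers only the four pre-K themes.

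Section {11d} asks all teachers, at the end of both years, about other trainings. Section {11c} gives implementation notebooks to intervention teachers and describes recordings of curriculum sessions. Section {20a} bases the treatment-on-the-treated estimate on take-up from the fidelity measures, and {20c} keeps intention-to-treat by initial assignment.

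**The concern.** The control arm's access to the programme opens before both follow-up outcomes are measured, and the article does not connect the two facts. A control child who spends kindergarten with a wait-list teacher who has accepted the training and delivers the programme is no longer an untreated comparator at T3 or T4. The route is visible in the design: a mixed class teaches both pre-K and kindergarten, so a child can stay with the same teacher. The same route lets an intervention child stay with a teacher who was trained in year 1.

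At stake is the meaning of the follow-up results. A null or reduced T3 difference could be fade-out or control exposure. A positive one could be persistence or continued delivery. Without exposure data for the second year, the trial could not tell these apart. The treatment-on-the-treated estimate at T3/T4 has a related weakness: if control take-up is taken as zero when it is not, its denominator is too large.

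**Working it through.** **1. Sequence.** The offer runs from September 2022 to June 2023 ({6b}). T3 is May-June 2023; T4 is September 2023 and March 2024 ({13}). T3 lies at the end of the offer window and T4 lies after it. T1 (May-June 2022) precedes it and is untouched.

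**2. Exposure route.** Mixed control classes: 14/32 = 0.4375. The other 18 control classes (18/32 = 0.5625) show no direct route through the child's own teacher. A child could still move to a trained teacher's class, since 64 classes share 50 schools. Through the child's own class, the exposed share c lies between 0 and 0.4375; the document does not say where.

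**3. The plan's own figure.** Sample size {14} gives 55 classes for 0.35 SD with 10 children per class. Alpha, power, the ICC used, R² and attrition are not given. Assume two-sided 5%, 80% power and R² = 0:

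J = 4(1.96 + 0.84)² × [ICC + (1 − ICC)/10] / 0.35²

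This gives 53.3 at ICC 0.12 and 55.6 at ICC 0.13. The stated 55 is compatible with the article's ICC range but cannot be uniquely reproduced. The figure is not in dispute; ICC 0.13 is used below because it comes close to it.

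**4. Dilution.** Assume a true, fully maintained effect of 0.35 SD, the full effect in exposed control children, and no added effect from a second year in the intervention arm. The contrast is then 0.35 × (1 − c). Power comes from the noncentral t with 62 df and variance 4[ICC + (1 − ICC)/10]/64.

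| Exposed share c | Contrast (SD) | Power, ICC 0.13 | Power, ICC 0.10 |
|---|---|---|---|
| 0 | 0.350 | 84% | 89% |
| 0.10 | 0.315 | 76% | 81% |
| 0.219 (half of the mixed control classes) | 0.273 | 64% | 70% |
| 0.4375 (all 14) | 0.197 | 38% | 43% |

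**5. Treatment-on-the-treated.** The Wald estimate is the intention-to-treat effect divided by the difference in take-up. At the ceiling, with intervention take-up of 1, the correct denominator is 1 − 0.4375 = 0.5625, and 0.197/0.5625 = 0.35. With control take-up set to zero, the estimate stays at 0.197.

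**6. Cost of restricting to single-level classes.** At ICC 0.10, unadjusted, with t quantiles on J − 2 df, the minimum detectable effect is 0.31 SD for 64 classes and 0.42 SD for 36. Power for 0.35 SD with 36 classes is about 65%, below the 70% that all 64 classes give even when half of the mixed control classes are fully exposed.

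**The case against.** The strongest reply is that exposure is possible but not shown. The training is an optional offer, it goes to teachers recruited at pre-K level, and the trial children are in kindergarten by then. Exposure needs three things: the child stays with or moves to a wait-list teacher, that teacher accepts, and the programme is delivered before T3. None is documented. This stands. A reader might infer from the dates alone that the control arm is partly treated at follow-up; the text supports only that it may be.

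A reader might also infer that mixed classes compare two years of programme with one. The article does not support this, because it limits the evaluated content to the four pre-K themes; continued delivery in year 2 is neither stated nor ruled out. That reading also does not fit the 0.20 SD figure, which assumes no contrast at all in mixed classes.

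Nor does the plan ignore class type. Randomisation was stratified by it, and {20b} already lists multi-level classes as a subgroup for the outcomes in {12}, which include follow-up. It does not, however, link that split to second-year exposure.

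Section {20c} promises to measure non-adherence from data gathered over the school year, and {11a} monitors well-being activities that control teachers start themselves. Neither names second-year delivery of this programme, and the question in {11d} concerns other trainings.

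Finally, intention-to-treat remains a valid randomised contrast, and control exposure to a beneficial programme would pull it towards no difference. That is correct, but it does not settle what the contrast should be called.

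**Conclusion.** The point holds in a limited form. Control-arm access precedes T3 and T4, a route to exposure exists in 14 of 32 control classes, and the article neither rules exposure out nor names a measure of it. The dilution of a 0.35 SD effect ranges from none to about 0.20 SD. The lower figure is a worst case for the own-class route: every child in the mixed control classes stays, every teacher delivers, and the full effect is gained. Power at that ceiling is about 38% (assumed ICC 0.13, 10 children per class, two-sided 5%, no covariate gain).

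T1 is unaffected. It would go too far to say that the follow-up questions cannot be answered: if no control child meets a wait-list teacher, nothing changes. What is unsupported is describing T3 and T4 as maintenance and superiority over an untreated control without knowing second-year exposure. This is an inexpensive improvement that changes what the trial can conclude from follow-up.

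**What to change.** 1. At T2 and T3, record for each child in both arms who the 2022-23 class teacher is, and whether that teacher was trained in and delivered this programme. The present second-year question covers other trainings only.
2. In {7} and {20a}, define the T3/T4 intention-to-treat contrast as the programme in the pre-K year versus the programme offered one year later. Claim maintenance only in light of the recorded exposure. Use take-up in both arms in any T3/T4 treatment-on-the-treated estimate.
3. Keep all 64 classes as the main T3/T4 analysis. Use the class-type split already planned in {20b}, with the 18 versus 18 single-level stratum as a pre-specified sensitivity analysis for maintenance. Making that stratum the main test is a debatable trade: it loses power and is not guaranteed free of exposure.

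The cost is one or two questionnaire items at contacts already scheduled, some wording, and a more modest T3/T4 claim.
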